### 5.3.2 Sensitivity

No sensitivity analysis is planned for primary endpoint.

### 5.3.3 Subgroup Analyses

No subgroup analyses are planned.

## 5.4 Exploratory endpoint analyses

### 5.4.1 Analysis of exploratory endpoints

1. To compare the concentration of plasma glucagon measured in pmol/L during induced hypoglycaemia (at 0, 15, 30 and 40min) in people with T1D prior to glibenclamide treatment, and at each dose step (at 0.3mg, 0.6mg and 3mg), to that of participants without diabetes (non-DM group).

A mixed-effects model (treatment x time-point) will be used to compare plasma glucagon values at each time-point (0, 15, 30 and 40min) during the hypoglycaemic phase of the hyperinsulinaemic hypoglycaemic clamp at baseline (T1D and non-DM group) and at each dose step (T1D group only).

Post-hoc analysis will be performed which will allow pairwise comparisons between the plasma glucagon values obtained at each time-point (T1D and non-DM group, see **Table 3**).

2. To compare the proportion of change in plasma glucagon concentration from euglycaemia to hypoglycaemia at each time point (0, 15, 30 and 40min) in T1D participants prior to treatment, and at each dose step (at 0.3mg, 0.6mg and 3mg) of glibenclamide, to that of participants without diabetes (non-DM group).

We will calculate the proportion of increase in plasma glucagon at each time point by taking plasma glucagon values at each time-point (0, 15, 30 and 40min) during the hypoglycaemic phase of the hyperinsulinaemic hypoglycaemic clamp divided by the value at the corresponding time-point during the euglycaemic phase.

A mixed-effects model (treatment x time-point) will be used to compare the proportion increase in plasma glucagon as dependent variable (i.e. plasma glucagon concentration during the hypoglycaemic phase vs plasma glucagon concentration during the euglycaemic phase) at each time-point (0, 15, 30 and 40min) as independent variable at baseline (T1D and non-DM group) and at each dose step (T1D group only).

Post-hoc analysis will be performed which will allow pairwise comparisons between the plasma glucagon values obtained at each time-point (see **Table 3**).

3. To compare the percentage of time spent in hypoglycaemia

**Table 1** (<4.0mmol/L of blood glucose) at each dose step (at 0.3mg, 0.6mg and 3mg) of glibenclamide, compared to baseline (T1D group only). Three separate paired t-tests will be used to compare 0mg vs 0.3mg, 0mg vs 0.6mg and 0mg vs 3mg. If the assumptions of t-test are not satisfied, then the percentages will be treated as proportion and a 2 proportions test will be used.

4. To compare the proportion of change in plasma glucagon levels measured in pmol/L at each time point 0, 15, 30 and 40min, (i.e. glucagon concentration at 0min during the hypoglycaemic phase divided by the glucagon concentration at 0min during the euglycaemic phase) from euglycaemia to hypoglycaemia in T1D participants prior to and following administration of a single 10 mg dose of oral dapagliflozin, to that of participants without diabetes (non-DM group).

Plasma glucagon values at each time-point (0, 15, 30 and 40min) during the hypoglycaemic phase of the hyperinsulinaemic hypoglycaemic clamp will be divided by the value at the corresponding time-point during the euglycaemic phase. A mixed-effects model (treatment x time-point) will be used to compare the proportion change in plasma glucagon (i.e. plasma glucagon during the hypoglycaemic phase vs plasma glucagon during the euglycaemic phase) after taking a single dose of dapagliflozin (T1D group only) versus baseline/no treatment (T1D and non-DM group).

Post-hoc analysis will be performed which will allow pairwise comparisons between the plasma glucagon values obtained at each time-point.

5. To compare the proportion of change in plasma somatostatin levels measured in pmol/L at each time point 0, 15, 30 and 40min (i.e. somatostatin concentration at 0min during the hypoglycaemic phase divided by the somatostatin concentration at 0min during the euglycaemic phase) from euglycaemia to hypoglycaemia in T1D participants prior to and following administration of a single dose of dapagliflozin 10mg, to that of participants without diabetes (non-DM group).

Plasma somatostatin values at each time-point (0, 15, 30 and 40min) during the hypoglycaemic phase of the hyperinsulinaemic hypoglycaemic clamp will be divided by the value of plasma somatostatin at the corresponding time-point during the euglycaemic phase.

A mixed-effects model (treatment x time-point) will be used to compare the proportion change in somatostatin (i.e. somatostatin during the hypoglycaemic phase vs. somatostatin during the euglycaemic phase) after taking a single dose of dapagliflozin (T1D group only) versus baseline/no treatment (T1D and non-DM group).

Post-hoc analysis will be performed which will allow pairwise comparisons using correlation [7] between the plasma somatostatin values obtained at each time-point.

6. To characterise the development of hypoglycaemic symptoms by listing self-reported hypoglycaemia symptoms and recording blood glucose value (mmol/L) at onset of self-reported hypoglycaemia symptoms (see **Table 4**[Error! Reference source not found.](#): Assessment of hypoglycaemia symptoms) during the induced hypoglycaemia at baseline, and during each dose of glibenclamide (at 0.3mg, 0.6mg or 3mg) and dapagliflozin.

A multilevel modelling approach (treatment x group) will be used to compare the onset of self-reported hypoglycaemic symptoms during the hyperinsulinaemic hypoglycaemic clamp between the group with and without diabetes.

7. To measure fasting plasma C-peptide levels (pmol/L) at the start of the hyperinsulinaemic hypoglycaemic clamp (T1D group only).

We will use descriptive statistics to describe fasting plasma C-peptide levels (pmol/L) at the start of the hyperinsulinaemic hypoglycaemic clamp (T1D group only). This will be in the form of mean (standard deviation) if data is normally distributed or median (interquartile range) if not normally distributed.

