## 1.2 Study Design

The LEGEND-D trial is a pilot, randomised cross-over, single-centre, non-blinded, clinical trial which aims to investigate the effect of 3 low doses of glibenclamide (0.3mg, 0.6mg and 3mg/day) assigned in all possible sequences followed by dapagliflozin (single dose of 10mg) on the plasma glucagon response during induced hypoglycaemia in people with type 1 diabetes, compared to non-diabetic individuals (**Figure 1**). The trial will be conducted by the Oxford Centre for Diabetes, Endocrinology and Metabolism (OCDEM) Clinical Research Unit (CRU) at the Churchill Hospital.

**Figure 1:** Trial flow chart

[figure not shown]

A summary timeline of the trial is shown on figure 1 above. For participants with T1D, the trial is divided into 5 steps, and involves 5 hyperinsulinaemic hypoglycaemic clamps. Once step 1 (no medication) has been completed, the participants with T1D will be randomised to a sequence of glibenclamide doses for the subsequent steps, followed by a single dose of 10mg dapagliflozin. There will be a washout phase of at least 48 hours between each step (the half-life of the glibenclamide suspension is 8 hours) [1]. Participants without diabetes will undergo a single hyperinsulinaemic hypoglycaemic clamp, as they will not receive any study medication.

The total daily dose as defined by the dosing schedule will be split into AM and PM as shown in

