## 5.3 Primary Endpoint Analysis

### 5.3.1 Primary Efficacy Analysis

To determine whether people randomised to glibenclamide at 0.3mg, 0.6mg or 3mg daily for 14-18 days can change the counter-regulatory plasma glucagon concentration measured in pmol/L at 40min during induced hypoglycaemia compared to baseline (pre-treatment) in T1D group only. We will use 3 separate paired t-tests to compare plasma glucagon concentration (pmol/L) at baseline and at each glibenclamide dose step i.e. 0mg vs 0.3mg, 0mg vs 0.6mg, and 0mg vs 3mg. We will also use linear random effects model [6] using plasma glucagon concentration (pmol/L) at each glibenclamide dose step as dependent variable and including treatment, period, and sequence of treatment to account for within-subject correlation to quantify the magnitude and direction of the change (increase/decrease). We will also adjust for age, gender, body weight, height, SBP, DBP and resting heart rate.

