## 8 Appendices

### 8.1 Appendix 1: Reporting Conventions

**Table 3 : Groups for comparison by oral glibenclamide dose in milligrams (mg)**

|     |     | non-DM | T1D |     |     |
|-----|-----|--------|-----|-----|-----|
|     |     | 0      | 0.3 | 0.6 | 3   |
| T1D | 0   | vs.    | vs. | vs. | vs. |
|     | 0.3 | vs.    | -   | vs. | vs. |
|     | 0.6 | vs.    | -   | -   | vs. |
|     | 3   | vs.    | -   | -   | -   |

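### The exploratory glucagon models in SAP 5.4.1 (items 1 and 2) omit period, so drift across the dose steps would widen the dose-versus-dose intervals; a minor point with a near-free fix

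*SAP*

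**What the plan says.** SAP 1.2 describes a cross-over in which the three glibenclamide doses are "assigned in all possible sequences followed by dapagliflozin", so there are six orders. Step 1 is untreated for everyone. After it, "the participants with T1D will be randomised to a sequence of glibenclamide doses for the subsequent steps". Dapagliflozin always comes last. Only steps 2, 3 and 4 are therefore in randomised order.

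SAP 5.3.1 specifies the random effects model for the primary endpoint as "including treatment, period, and sequence of treatment to account for within-subject correlation".

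SAP 5.4.1 specifies less. Item 1: "A mixed-effects model (treatment x time-point) will be used to compare plasma glucagon values at each time-point". Item 2: "A mixed-effects model (treatment x time-point) will be used to compare the proportion increase in plasma glucagon as dependent variable". Time-point there means 0, 15, 30 and 40 minutes within a clamp, so it does not stand in for period. Both items then say: "Post-hoc analysis will be performed which will allow pairwise comparisons between the plasma glucagon values obtained at each time-point", and both refer to Table 3. That table has ten cells, three of which compare one glibenclamide dose with another. Outside 5.3.1, period appears only in descriptive reporting (5.1 and 5.2).

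**The concern.** The three dose-versus-dose cells are the only contrasts in Table 3 that are both within-person and in randomised order. They are the ones for which period can be estimated separately from treatment. If the glucagon response changes over repeated clamps, a model without period counts that change as noise. The standard error is then too large and power is lost.

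Twenty participants also cannot be spread evenly over six sequences. In any one realised allocation, a small part of the drift can therefore move a dose contrast.

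There is a consistency problem too. At 40 minutes, item 1 analyses the same glucagon values as the primary model. The same dose contrast could be reported twice, once adjusted for period and once not, with different intervals.

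**Working it through.** **Inputs from the SAP.** Section 1.3.4 gives a T1D mean of 5.54 pmol/L, SD 2.14 pmol/L, a 30% increase, 80% power, and 20 T1D participants including 5% dropout. Section 5 gives alpha 0.05, taken as two-sided. The 30% difference is 0.30 × 5.54 = 1.662 pmol/L.

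**Assumed inputs.** The SAP gives neither the within-person correlation (ρ) nor the drift per step (d, taken as linear). I use ρ = 0.35 and 0.5, and d from 0 to 1.0 pmol/L.

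**The plan's own figure.** The 20 participants cannot be confirmed without ρ. A paired t-test with SD of the difference 2.14 × √(2(1 − ρ)) reaches 80% power with 19 pairs at ρ = 0.35, and 19/0.95 = 20. This is why 0.35 is used below. At ρ = 0.5 it needs 16 pairs. The 80% in the plan refers to glibenclamide versus baseline; no power is stated for dose versus dose.

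**Variance.** Within one participant, linear drift over three steps deviates from its own mean by −d, 0 and +d, a sum of squares of 2d². The item 1 model has four T1D clamps per person (untreated plus three doses), so about three within-person degrees of freedom. Leaving period out therefore adds about (2/3)d² to the residual variance. With σw² = 2.14²(1 − ρ), the standard error is multiplied by √(1 + (2/3)d²/σw²).

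| d (pmol/L per step) | ρ = 0.35, σw² = 2.98 | ρ = 0.5, σw² = 2.29 |
|---|---|---|
| 0.5 | √(1 + 0.167/2.98) = 1.03 | √(1 + 0.167/2.29) = 1.04 |
| 0.75 | √(1 + 0.375/2.98) = 1.06 | √(1 + 0.375/2.29) = 1.08 |
| 1.0 | √(1 + 0.667/2.98) = 1.11 | √(1 + 0.667/2.29) = 1.14 |

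At ρ = 0.35 the standard error of a dose contrast with period in the model is about √(2 × 2.98/20) = 0.55. Without period, at d = 1.0, it is about 0.55 × 1.11 = 0.60.

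**Power.** This was simulated for a dose difference of 1.662 pmol/L at one time-point, with 20 participants over six near-even sequences and the untreated clamp included.

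| ρ | d | Without period | With period |
|---|---|---|---|
| 0.35 | 0 | about 85% | about 85% |
| 0.35 | 0.5 | about 84% | about 85% |
| 0.35 | 0.75 | about 82% | about 85% |
| 0.35 | 1.0 | about 80% | about 85% |
| 0.5 | 1.0 | about 88% | about 93% |

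Without period, the actual type I error at d = 1.0 is about 3% instead of 5%.

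**Realised shift.** For any two doses, the six orders give step differences of ±1, ±1 and ±2. Under a 4,4,3,3,3,3 split, the balanced 18 participants cancel and the two extra ones contribute at most (2 + 1)/20 = 0.15 steps. At d = 1.0 this is 0.15 pmol/L, about a quarter of the standard error of 0.55 to 0.60. Averaged over randomisation the shift is zero.

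**The case against.** The case for leaving the text alone has real weight.

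- **Reach.** Items 1 and 2 are exploratory, and their stated aim is comparison with the non-DM group. Dose versus dose is three of ten post-hoc cells. At 40 minutes the 5.3.1 model can already give period-adjusted dose contrasts for absolute glucagon, so the gap is the earlier time-points and the ratio. This stands, and it limits the importance of the point.
- **Size of drift.** A drift of 1.0 pmol/L per step is 18% of the 5.54 mean (1.0/5.54). Over steps 2 to 4 it totals 2.0 pmol/L, more than the 1.66 the trial is sized on. Nothing in the SAP suggests drift of that size. This also stands.
- **Shorthand.** The bracketed term might name only the factors of interest. That is possible, but where period was wanted, in 5.3.1, the SAP named it. An analyst following 5.4.1 literally would leave it out.

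Three stronger readings are tempting and are not supported.

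- A reader might infer that the dose contrasts are biased or that false dose-response claims become likelier. Over randomisation they are unbiased, and with near-even sequences the error is conservative.
- A reader who models only the three dose clamps would find about 74% versus 84% power at d = 1.0 and ρ = 0.35. Item 1 plans to include the untreated T1D clamp, which roughly halves that loss.
- A reader might extend the point to comparisons with the untreated clamp, dapagliflozin or the non-DM group. Step and treatment coincide in the first two, and the controls have a single clamp, so a period term cannot help there.

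**Conclusion.** The omission is real, and adding period is a minor improvement at almost no cost. It affects only the three dose-versus-dose cells of Table 3. For item 1 at one time-point and ρ = 0.35, the loss is about 1 to 2 points of power at a drift of 0.5 pmol/L per step, about 3 at 0.75 and about 5 at 1.0. At 1.0 the standard error is 11 to 14% too large for ρ of 0.35 to 0.5. With no drift, adding the term loses nothing measurable.

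These sizes rest on an assumed ρ, an assumed linear drift, a 30% dose-to-dose difference borrowed from the primary endpoint, and near-even sequences. The last matters for the direction. Under simple randomisation the imbalance between two doses has an SD of √(2/20) = 0.316 steps, so part of the drift would appear as real scatter in the estimate and not only as an overstated standard error. The joint model over four time-points was not simulated. Item 2 analyses a ratio; the mechanism carries over, but no figure is claimed for it.

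**What to change.** In SAP 5.4.1 items 1 and 2, add period (step 2, 3 or 4) as a three-level factor to the mixed model, with period × time-point if contrasts are reported at each time-point. Code it to sum to zero over steps 2 to 4, and set it to zero for the untreated step 1 clamp and for the non-DM controls. With this coding the single-time-point design (untreated T1D, three doses, controls and two period columns) has full rank, 7 of 7. Take the Table 3 dose-versus-dose comparisons from this model.

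Add a sentence that the period term does not remove the order confounding of comparisons with the untreated clamp, with dapagliflozin or with the non-DM group.

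The cost is a line or two of SAP text and two model degrees of freedom, or up to eight (2 × 4) with period × time-point. No new data are needed, because the step is already recorded for the primary model.

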During these challenges, we will gradually drop participants' blood sugar from a normal level (around 6 mmol/L) to a lower level (around 2.5mmol/L) for 40 minutes. While this is a well-established procedure, this change in blood sugar can be stressful and participants without diabetes will probably not have experienced the symptoms before. We will screen all participants for high risk conditions, and monitor them closely during

the entire procedure. We will use a continuous glucose monitor during the study in participants with T1D. All participants will need to attend the OCDEM Clinical Research Unit at the Churchill Hospital, Oxford for an initial screening visit. This will be followed by 8 study visits over a period of 8-10 weeks (divided into around 2-week blocks) for the people with T1D, and the people without diabetes will have just 1 study visit.

The purpose of this statistical analysis plan (SAP) is to outline the planned analyses to be performed in the LEGEND-D trial. The SAP will be amended if changes to the planned analyses are required, and will be finalised before the database lock for this study. Exploratory post-hoc or unplanned analyses not necessarily identified in this SAP may be performed on these data as required. These analyses will be clearly identified in the statistical report for the study.

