### **1.1.2 Exploratory Objectives**

1. To compare the plasma glucagon response during induced hypoglycaemia in people with T1D prior to glibenclamide treatment, and at each dose step, to that of participants without diabetes (non-DM group).
2. To compare the increase in plasma glucagon from euglycaemia to hypoglycaemia in T1D participants prior to treatment, and at each dose step of glibenclamide, to that of participants without diabetes (non-DM group).
3. To compare the percentage of time spent in hypoglycaemia (

**Table 1)** at each dose step of glibenclamide, compared to baseline (T1D group only)

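### Exploratory items 2, 4 and 5 divide each hypoglycaemic hormone value by a single euglycaemic sample with the same minute label, which mixes euglycaemic trend and avoidable noise into the time-specific ratios

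*SAP*

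**What the plan says.** SAP section 1.1.2 sets the objective behind item 2: "To compare the increase in plasma glucagon from euglycaemia to hypoglycaemia in T1D participants prior to treatment", and at each glibenclamide dose, against the non-diabetic group. Objectives 4 and 5 do the same for dapagliflozin, with glucagon and somatostatin.

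Section 5.4.1 turns this into ratios. Item 2 forms them "by taking plasma glucagon values at each time-point (0, 15, 30 and 40min) during the hypoglycaemic phase" of the clamp, each "divided by the value at the corresponding time-point during the euglycaemic phase". Item 4 repeats the rule and gives an example: "glucagon concentration at 0min during the hypoglycaemic phase divided by the glucagon concentration at 0min during the euglycaemic phase". In item 5 each somatostatin value "will be divided by the value of plasma somatostatin at the corresponding time-point during the euglycaemic phase".

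The ratio is then modelled over time. For item 2, "A mixed-effects model (treatment x time-point) will be used to compare the proportion increase in plasma glucagon as dependent variable", followed by pairwise comparisons at each time-point. Items 4 and 5 use the same form of model.

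The Introduction describes the clamp as lowering "blood sugar from a normal level (around 6 mmol/L) to a lower level (around 2.5mmol/L) for 40 minutes", so euglycaemia comes first and hypoglycaemia second. Section 6.2 identifies no data transformation, and section 5.4.2 plans no sensitivity analysis for exploratory endpoints.

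**The concern.** A change from euglycaemia to hypoglycaemia needs a euglycaemic reference level. The plan uses four references per clamp, matched on a minute label. Minute 30 of the first phase and minute 30 of the second are neither simultaneous nor otherwise paired by anything the SAP states.

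This has two consequences.

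- **Time-course.** Numerator and denominator both change with the label, so a trend in the ratio may come wholly from the euglycaemic phase. The model would report it as a time-point effect, or as a treatment by time-point interaction if the trend differs between groups or visits.
- **Noise.** The rule requires a euglycaemic sample at all four labels, yet each ratio uses only one of them. A noisy denominator widens the spread of each time-specific ratio. On the untransformed scale it also pushes the mean ratio upward. With 20 T1D participants and 10 controls there is little precision to spare.

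**Working it through.** The SAP states no figure for this point, so there is none to reproduce.

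**Inputs.** The ratio rule and the four labels come from section 5.4.1. For scale only, the euglycaemic start is set at 5.54 pmol/L and the flat hypoglycaemic level at 7.2 pmol/L. The first figure is the T1D mean in section 1.3.4, which is itself a value at hypoglycaemia. The second is about 30% higher, the effect in that section. The true ratio is 7.2/5.54 = 1.30. Assumed, because the SAP gives neither: a linear euglycaemic fall of 10–30% over 40 minutes, and a sample-to-sample CV of 10–30%. Simulated figures use 400,000 clamps per setting with log-normal error.

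**1. Drift within one clamp.** With flat hypoglycaemic hormone, the 40-minute ratio over the 0-minute ratio is 1/(1 − drift):

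- 10% fall: 1/0.90 = 1.11 (+11%)
- 20% fall: 1/0.80 = 1.25 (+25%)
- 30% fall: 1/0.70 = 1.43 (+43%)

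At CV 20% and a 20% fall, the simulated same-label ratios run 1.35, 1.46, 1.59, 1.69. With the four-sample mean as denominator they stay at 1.47.

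**2. Same-minute comparison of two doses or groups, A and B.** If both share the euglycaemic time pattern g(t), then [H_A/(E_A·g)] / [H_B/(E_B·g)] = (H_A/E_A)/(H_B/E_B). The pattern cancels as a factor. On the raw difference scale it rescales a real difference by 1/g(t), but cannot create one where none exists.

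**3. Drift in one group only.** For a 20% linear fall the euglycaemic factors at 0, 15, 30 and 40 minutes are 1, 0.925, 0.85 and 0.80. Their mean is 3.575/4 = 0.894.

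| Denominator | 0 | 15 | 30 | 40 | Average |
|---|---|---|---|---|---|
| Same label | 0% | +8% | +18% | +25% | +12.7% |
| Four-sample mean (1/0.894) | +11.9% | +11.9% | +11.9% | +11.9% | +11.9% |

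The mean denominator removes the false interaction. It leaves almost the same bias in the overall effect and introduces it at minute 0.

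**4. Noise per time-specific ratio, log scale.** Let each sample have error variance s².

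- Independent errors: same-label variance is s² + s² = 2s², and four-sample-mean variance is s² + s²/4 = 1.25s². The ratio is 2/1.25 = 1.6.
- Within-phase correlation r: the ratio is 2/[1 + (1 + 3r)/4], which gives 1.36 at r = 0.3, 1.23 at r = 0.5 and 1.08 at r = 0.8.
- 40-minute minus 0-minute contrast, independent errors: 4s² against 2s².

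**5. Raw scale, no drift, independent errors (simulated).**

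| CV | SD, same label | SD, mean | Mean ratio, same label | Mean ratio, mean |
|---|---|---|---|---|
| 10% | 0.186 | 0.146 | 1.313 | 1.303 |
| 20% | 0.387 | 0.295 | 1.352 | 1.313 |
| 30% | 0.615 | 0.450 | 1.417 | 1.329 |

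The true ratio is 1.30. The same-label means agree with 1.30 × (1 + CV²): at CV 30%, 1.30 × 1.09 = 1.417.

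**6. Effect averaged over the four time-points.** On the log scale the variance is s²/4 + s²/4 = 0.5s² under either rule. On the raw scale at CV 20% the SD is 0.193 against 0.186.

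**The case against.** The best defence is that the rule is explicit, reproducible and consistent across three items, and that the planned comparisons are between doses and groups. Table 3, which item 2 cites for its pairwise comparisons, lists only dose and group pairs. Common drift cancels there as a factor (step 2). Item 1 already analyses the undivided hypoglycaemic glucagon values at all four minutes for baseline, the glibenclamide doses and the controls. The SAP gives neither euglycaemic drift nor within-phase variation. All of this stands and limits the point.

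Three stronger readings are tempting, and the SAP supports none of them.

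- A reader might take the 11–43% as bias in the dose or group comparisons. Those figures are a 40-versus-0-minute contrast within one clamp under assumed drift.
- A reader might infer that every confidence interval is widened. Step 6 shows nothing lost on the log scale, and little on the raw scale, for the time-averaged effect.
- A reader might treat the dapagliflozin visit as proof of differential drift, because section 1.2 says glucagon is raised 2 hours after the dose and peaks at 4 hours. This makes such drift plausible. It does not show drift within the euglycaemic phase, because the SAP does not time the phases against the dose.

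The defence does not supply a reason for the pairing. Nor does it answer the loss of precision in the time-specific ratios, which the plan chooses to model.

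**Conclusion.** The point holds as a minor improvement to exploratory items 2, 4 and 5. The same-label denominator has no stated basis and lets euglycaemic trend into the time-point effect. It reaches the treatment by time-point interaction only if the trend differs by group or visit. It costs up to 1.6 times the log variance per time-specific ratio with independent errors, about 1.2 times at a within-phase correlation of 0.5, and less at higher correlation. It also adds upward bias to the raw ratio. The directions follow from algebra, but every drift and noise size is assumed.

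It would be wrong to conclude that averaging the denominator removes bias from differential drift. Step 3 shows that bias moving from the interaction into the overall treatment or group effect at nearly the same size. The primary endpoint, a 40-minute concentration, and item 1 use no ratio and are untouched.

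**What to change.** In section 5.4.1, items 2, 4 and 5:

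1. Use one denominator per clamp, the mean of its four euglycaemic samples (0, 15, 30 and 40 minutes). Divide each hypoglycaemic value by it.
2. Add a clamp-level (participant-by-visit) random effect, or an equivalent within-clamp correlation, to the mixed model. With independent errors the shared denominator alone gives two log ratios of one clamp a correlation of 0.25/1.25 = 0.2. These items name only a treatment by time-point mixed-effects model, and a participant effect alone would not capture this in participants with several clamps.
3. Report the euglycaemic values by time-point, group and visit. If they drift differently, the mean is a compromise reference, and readers need to see how much of an overall difference could come from the denominator.

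The cost is SAP wording, one extra model term and one descriptive table. No new samples are needed, since the present rule already requires all four euglycaemic values.
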